## Background

Laparoscopic Roux-en-Y gastric bypass (RYGB) has in recent years been the standard operation in Swedish bariatric surgery. The operation is well studied and we have a good idea of the expected result regarding weight, BMI, comorbidities, and it can be performed with a low complication rate. However, this does not mean that the surgical method is without challenges, and above all there is a small but important group of patients with prolonged morbidity after the procedure. Due to the bypassing of the duodenum and proximal jejunum, there is also a concern for long-term risk of various types of deficiency conditions.

Laparoscopic sleeve gastrectomy (SG) is a relatively recently introduced surgical method that in recent years has gained rapid and wide spread internationally and is currently the most commonly used obesity surgical technique in the United States. However, there are not results from long-term studies to the same extent as for RYGB. However, the reported data indicate good results regarding weight development and resolution of comorbidity up to a few years after the operation, although to a somewhat lesser extent compared to after RYGB. There are currently no long-term data presented for SG.

RYGB has been associated with a non-negligible risk of internal herniation with small bowel obstruction, which appears to affect at least 10% of patients operated on without closure of mesenteric defects, and despite closure a risk remains. This risk of internal herniation does not exist with SG. Another advantage of SG is that it avoids the problems with the Jejunojejunostomy (JJ), which seems to be part of the rare but difficult to treat morbidity after RYGB. There is also probably a slightly lower risk of vitamin and mineral deficiency because the duodenum and proximal jejunum are not bypassed. However, there are data that suggest that problems with gastro-oesophageal reflux may occur or worsen after SG and that continuous acid-suppressing treatment may be necessary. There are also indications that revisional surgery rates may be higher after SG, e.g. due to unsatisfactory weight development over time.

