| Death                                  | Death associated with bariatric surgery.                                                                                                                                                                                                                                                      |
| Intervention under general anesthesia  | Complication according to Clavien-Dindo 3b or higher associated with the bariatric intervention (excluding gallstone interventions, preexisting hernia at bariatric surgery, and plastic surgery for removal of excess skin). A sub analysis of negative diagnostic laparoscopies is planned. |
| Admission to intensive care unit (ICU) | Admission to ICU due to complications from bariatric surgery.                                                                                                                                                                                                                                 |
| Revision surgery                       | Change of surgical method; reversal or significant change of the original method. Revision surgery will be performed according to clinical practice. The indication for revision surgery (e.g. unsatisfactory weight loss or gastro-esophageal reflux) should be                              |

|                                           |                                                                                                                                                                                                                                           |
|-------------------------------------------|-------------------------------------------------------------------------------------------------------------------------------------------------------------------------------------------------------------------------------------------|
|                                           | documented.                                                                                                                                                                                                                               |
| In-hospital care                          | Due to complications related to the surgery (excluding observation without diagnosis for less than 24 hours)                                                                                                                              |

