### 5.2 Principles of analysis

171

172 The primary conclusions from this study will be based on analyses conducted under the principle of  
 173 intention-to-treat. Thus, all randomised patients, with exception to those who withdraw their  
 174 consent, will be included in the analyses. In the analysis, it is further assumed that all randomised  
 175 patients receive the treatment they were randomised to.

Those patients who are randomised but withdraw their consent to use their data will not be included in any analyses. Only the information that they were enrolled into the study and withdrew their consent, and the original treatment group to which they were allocated, will be reported.

Data from all operating clinics (centres) will be pooled in primary analyses. The study will be conducted under a common protocol for each participating clinic with the intention to pool the data for analyses.

In addition to the primary analysis using intention-to-treat population, exploratory analyses using per-protocol (as treated) populations will be conducted for all outcome variables.

For primary outcomes, two-sided 2.5% significance level will be used to identify statistically significant results. The corresponding confidence intervals to be reported will be 97.5% confidence intervals. The use of 2.5% significance is due to two primary endpoints.

There will not be any formal interim analyses on primary outcomes. The safety and Data Monitoring Committee has a responsibility to monitor adverse events and complications during the study follow-up period.

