### 5.3 Statistical analyses

Summary tables (descriptive statistics and frequency tables) will be provided for all baseline variables, outcome variables, and safety variables, as appropriate. Continuous variables will be summarized with descriptive statistics (n, mean, standard deviation, range, and median). Frequency counts and percentage of subjects within each category will be provided for categorical data.

Incidence of substantial adverse events will be analysed with time-to-event models. Time to first substantial adverse event (as defined in chapter 4 Study outcomes) from primary surgery will be recorded. Kaplan-Meier estimates of cumulative incidence of adverse events will be calculated in both treatment groups. Treatment effect will be calculated as a hazard ratio, together with corresponding confidence interval and p-value for the test of equal hazard ratio, from Cox proportional hazard regression model. The proportionality assumption of the Cox models will be evaluated graphically using "log-log" plots.

The primary conclusions will be based on a model which includes study centre as a covariate together with indicator for treatment. Explorative analyses will be conducted using sex, age, body mass index, smoking and diabetes at baseline as covariates.

For non-inferiority, the difference in weight loss between treatment groups and its confidence interval will be calculated and evaluated against the non-inferiority margin of 5%. The weight loss difference at 5-year follow-up will be estimated with a multilevel mixed-effect regression models utilizing body weight measurements at all available time points. This model takes into account the repeated measurements nested within persons over time. All randomized patients except those who have withdrawn their consent will be included in this analysis, independent of availability of body weight data during the follow-up. The primary conclusions will be based on a model which includes study center in addition to indicator for treatment.

For secondary outcomes, incidence of comorbidities during the follow-up will be evaluated with time-to-event models, and for continuous variables mixed-effect regression models will be used to evaluate differences between the treatment groups.

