#### 5.4 Study follow-up and missing data

For evaluation of incidence of severe adverse events, it is expected that the coverage will be close to 100% as these are to be collected through national register linkage. Patients who withdraw consent will be censored right after withdrawal in time-to-event models. Patients who emigrate from Sweden or die before the end of 5-year follow-up will be censored at the time of emigration and date of death, respectively. All other patients not experiencing substantial adverse events during the study follow-up will be censored at the date of individual 5-year follow-up. The primary conclusions of the study will be based on analyses conducted on all randomized patients (with exception of those who withdraw their consent) under the principle of intention-to-treat.

For evaluation of non-inferiority, a sensitivity analysis will be conducted using both multiple imputation of missing body weight data, as well as last observation carried forward (LOCF) imputation. The results of these analyses will be reported together with results of the primary analysis.

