## Appendix:

The unforeseen global Covid-19 pandemic resulted in that almost all elective benign surgery in Scandinavia was cancelled from March 2020. Thus, the pandemic had severe consequences on the recruitment to the BEST trial during 2020-2021.

During autumn of 2021 the BEST steering committee decided to perform an additional analysis of the power for primary endpoints.

Additional information (Courcoulas et al, JAMA Surg 2020 March; Howard et al, JAMA Surg 2021 Dec) revealed that the risk of any of the predefined substantial adverse events after bariatric surgery is higher than previously anticipated in the revised power calculation, i.e. >25% instead of 13%. These figures were confirmed in an analysis of real-world data from the bariatric national quality register SOReg in Sweden which registered all patients undergoing sleeve or bypass in Sweden since 2007.

An independent statistician performed the analysis based on information above, but also on 2-year data in BEST. In conclusion, it was stated:

Two post hoc power analyses were conducted based on the data from February 2022:

*1. Weight reduction. In the protocol the following is stated "This sample size will also have >95% power to evaluate non-inferiority of 5% weight loss difference over 5 years between the two groups, assuming 15 kg standard deviation in weight loss over follow-up with two-sided 2.5% significance level.". The post hoc power calculation is based on the two-year follow up data where an average weight loss for all patients (both groups, N=1031) of 29.3 kg was attained with a Sd=21.6. Given a loss to follow up of 20% from 2 year follow up to the 5-year follow up the sample size is assumed to be  $(1031 \cdot 0.80)/2 = 413$  patients per group. With a non-inferiority level of 5 kg weight loss the power is found to be 90% if  $n=393$  per group, and 95% if  $n=486$  per group (<https://www.sealedenvelope.com/power/continuous-noninferior/>).*

*2. Substantial adverse events. This post hoc power calculation is for a superiority test where the rate is assumed to be 25% for the gastric bypass at 5 years and sleeve would have a 35% lower level, i.e.  $25\% \cdot 0.65 = 16.25\%$ . Given a sample of  $n=413$  per group the post hoc power will then be 87.5%.*

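### No planned sensitivity analysis tests whether weight non-inferiority survives if SG patients with missing 5-year weights did worse than predicted

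*Combined protocol and SAP*

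**What the plan says.** Main SAP section 5.3 estimates the 5-year weight difference with "multilevel mixed-effect regression models utilizing body weight measurements at all available time points". All randomised patients enter except those who withdraw consent, "independent of availability of body weight data during the follow-up". Section 3.4 schedules weights at 6 weeks and at 1, 2 and 5 years, so there is no visit between years 2 and 5.

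For missing weights, section 5.4 names two analyses: a "sensitivity analysis will be conducted using both multiple imputation of missing body weight data, as well as last observation carried forward (LOCF) imputation". It gives no imputation model, no shift parameter, no reference-based method and no tipping point.

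The Appendix plans on substantial missingness: "Given a loss to follow up of 20% from 2 year follow up to the 5-year follow up". The protocol, under Primary outcome measure, makes weight stability at five years part of the primary question. Its Background reports indications that "revisional surgery rates may be higher after SG, e.g. due to unsatisfactory weight development over time".

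**The concern.** A sensitivity analysis for missing data is useful when it departs from the primary assumption in a direction that could overturn the conclusion. Here the conclusion at risk is that SG is not worse than gastric bypass (GBP) by more than the margin. The direction to test is therefore that SG patients with no 5-year weight did worse than the model predicts.

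Neither planned analysis does this. A mixed model fitted by likelihood assumes missing at random. Multiple imputation in its usual form assumes the same, so it should return roughly the same answer. LOCF makes a different assumption, but not a stringent one for this question. A patient last seen at year 2 is given the 2-year weight at year 5, which assumes no change over the interval in which weight stability is to be judged. If SG regains more than GBP after year 2, LOCF makes the arms look closer than they are.

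At stake is how far a non-inferiority claim on a co-primary endpoint can be called robust. Agreement between the primary model, multiple imputation and LOCF would look reassuring without having tested the scenario of most concern.

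**Working it through.** **Inputs.** From the SAP Appendix: SD 21.6 kg (2-year data, both groups together), N = 1031, 20% loss from year 2 to year 5, 413 per group, margin 5 kg. From SAP section 5.2: two-sided 2.5% level, hence 97.5% intervals (z = 2.2414).

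**Reproducing the plan's figures.** 1031 × 0.80 / 2 = 412.4, rounded up to 413. The Appendix gives 393 per group for 90% power and 486 for 95%. With n = 2(z_α + z_β)² × 21.6² / 5² and one-sided 2.5%:
- 90%: 2 × (1.960 + 1.282)² × 18.66 gives 393.
- 95%: 2 × (1.960 + 1.645)² × 18.66 gives 486.

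Both match, but only at one-sided 2.5%. The SAP's two-sided 2.5% is one-sided 1.25% and needs 464 and 564. That is a separate matter; the SAP's own level is used below.

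**Room to the margin.** SE = 21.6 × √(2/413) = 1.50 kg. Half-width = 2.2414 × 1.503 = 3.37 kg. Room at an estimated difference of 0 is 5 − 3.37 = 1.63 kg.

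**Tipping point.** Let m be the share of SG patients with imputed 5-year weights, d the estimated SG deficit under missing at random, and δ the extra weight of missing SG patients beyond prediction. The shift moves the SG mean by m × δ, so the limit reaches the margin at δ = (5 − 3.37 − d) / m. Example: (1.63 − 1.0) / 0.20 = 3.2 kg.

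| Missing in SG | d = 0 | d = 0.5 | d = 1.0 | d = 1.5 |
|---|---|---|---|---|
| 20% (Appendix) | 8.2 kg | 5.7 kg | 3.2 kg | 0.7 kg |
| 30% (assumed) | 5.4 kg | 3.8 kg | 2.1 kg | 0.4 kg |
| 40% (assumed) | 4.1 kg | 2.8 kg | 1.6 kg | 0.3 kg |

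The standard error is held at 413 per group throughout.

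**If precision is better (m = 20%).**
- If imputation recovered the full information of 515 per arm, the half-width is 3.02 kg and the room 1.98 kg. The tipping shift is 1.98 / 0.20 = 9.9 kg at d = 0 and 0.98 / 0.20 = 4.9 kg at d = 1.0.
- The 1031 is a February 2022 count, while 1752 were enrolled. If 80% of all 1752 had a 5-year weight (assumed), n = 1752 × 0.80 / 2 = 701 per group, SE = 1.15 kg and half-width 2.59 kg. The shifts become 2.41 / 0.20 = 12.1 kg and 1.41 / 0.20 = 7.1 kg.

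**LOCF.** With equal missingness by arm, a share m carried forward from year 2 and extra SG regain g, LOCF understates the deficit by m × g. With m = 20% and g = 0, 2, 3 or 5 kg (all assumed), that is 0, 0.4, 0.6 or 1.0 kg. If the true deficit equalled 5 kg, the chance that the LOCF analysis declares non-inferiority (515 per arm) would be 1.25%, 2.6%, 3.6% or 6.7%. These figures concern LOCF only, not the primary analysis.

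**The case against.** A reader might infer that the two planned analyses cannot challenge non-inferiority at all, or that both pull the arms together. The documents do not support that. The imputation model is unspecified, not stated to be missing at random. The protocol also refers to a separate analysis plan for each publication, which is not shown and might specify it. Imputation under missing at random has no inherent pull towards equality. LOCF biases the difference only if late regain or missingness differs by arm, and the documents give no such figures by arm. LOCF can also count against SG: if more SG patients drop out early, a baseline or 6-week weight carried forward understates their loss.

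A reader might also infer that weights after conversion to another operation are wrongly credited to SG. That does not stand as an error. The primary analysis is by intention to treat and assumes that all randomised "patients receive the treatment they were randomised to". Keeping observed weights in the allocated arm is a legitimate treatment-policy question. Revision surgery ("Change of surgical method; reversal or significant change of the original method") is itself a component of the other primary endpoint, so a failing sleeve that is revised can count against SG there. Reflux is also a listed indication, so not every revision reflects poor weight loss. The SAP further plans that "exploratory analyses using per-protocol (as treated) populations will be conducted for all outcome variables". What remains is a gap in definition: the handling of weights after revision is implied, not stated, and the effect of a conversion on per-protocol status is not given.

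It is also fair that every magnitude here except the 20% loss and the Appendix inputs is assumed. None of this supplies the missing analysis.

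**Conclusion.** The point holds in a limited form. The primary weight analysis is not invalid, and the planned analyses are not shown to favour SG. They are poorly suited to testing the claim, because none asks what happens if missing SG patients did worse than predicted.

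On the Appendix inputs with 20% missing, the claim would survive a shift of up to 8.2 kg at an estimated difference of 0, but only 3.2 kg at a deficit of 1.0 kg and 0.7 kg at 1.5 kg. The result could therefore be sturdy or fragile, and the plan as written would not show which.

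These figures assume the 2-year SD applies at year 5, shift the SG arm only, and use the Appendix's 5 kg margin. The main text states 5%, and the documents give no mean baseline weight to convert it. A larger final sample would raise the tipping shifts; more missing data would lower them. This should be changed before the 5-year analysis.

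**What to change.** In main SAP section 5.4:

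1. Specify the imputation model (variables, and whether imputation is done by arm).
2. Add delta-adjusted multiple imputation that shifts imputed SG 5-year weights over a prespecified range, in the unit of the margin. Fix and justify the range before 5-year weights are compared by arm.
3. Report the shift at which the 97.5% limit crosses the margin, beside the primary intention-to-treat result, and comment on whether a shift of that size is plausible.
4. Keep LOCF as a secondary analysis if wished; it need not be deleted.

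For clarity only: state that weights after revision stay in the allocated arm in the intention-to-treat analysis, and define per-protocol status after conversion in the exploratory analysis of section 5.2.

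The cost is SAP wording and a little programming, with no new data collection and no change to the primary analysis. The downside for the sponsor is that the non-inferiority claim may look less robust.

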#### 5.5 Timing of analyses

Participant recruitment is planned to be completed by June 2019. Five-year follow-up will be completed for all participants during summer of 2024. Data-preparation will be completed by December 2024. Analyses and the results on primary outcomes will be reported during year 2025.

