## 3. Study Design

### 3.1 Overview

This is a randomized, Scandinavian multi-centre study comparing the two most abundant bariatric surgery techniques worldwide; laparoscopic gastric bypass (GBP) and laparoscopic sleeve gastrectomy (SG). Study design is parallel group study with 1:1 allocation between GBP and SG.

To be invited to participate in the study as a collaborating centre, the operating bariatric clinic has to perform at least 100 bariatric surgeries annually, report to the Scandinavian Obesity Surgery Registry (SOREg) and be able to meet all criteria set in the project plan. The study, to be conducted at approximately 20 bariatric surgery clinics in Sweden and Norway, will include 2100 obese patients approved for bariatric surgery (1050 patients to be operated with SG and 1050 with GBP).

89 The follow-up time for the primary objectives is 5-years.

90

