Taking information above into account and in the interest of not prolonging inclusion period unnecessarily the trial steering committee took a decision to stop inclusion in BEST during spring 2022 (final date 31st of March). At termination of inclusion the number of participants that had been included and operated in BEST were 1752. The trial DSMC reviewed and supported the decision before termination of recruitment to the BEST trial.

1

2

3 Statistical analysis plan for:

4

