#### 166 5.5 Timing of analyses

167

168 Participant recruitment was completed on March 31st, 2022. Six-week follow-up was completed for  
169 all participants in May 2022. Data-preparation will be completed by September 2022. Analyses and  
170 the results on primary outcomes will be reported during spring 2023.

171

172    **Version history:**

173    version 4; Date: September 22th 2022: Tables of variables for baseline and surgical data added.

174    version 3; Date: September 20th 2022: Details regarding the statistical analyses added.

175    version 2; Date: September 15th 2022: Editing, removal of data preparation information.

176    version 1; Date: June 6th 2022: First draft.

177

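### SAP v5 section 5.5 still carries an analysis timetable built on recruitment ending in June 2019, although inclusion ended on 31 March 2022 and five-year follow-up cannot be complete before 2027

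*Combined protocol and SAP*

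**What the plan says.** SAP v5 section 5.5 gives four linked statements.

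- Recruitment: "Participant recruitment is planned to be completed by June 2019".
- Follow-up and data: "Five-year follow-up will be completed for all participants during summer of 2024. Data-preparation will be completed by December 2024".
- Reporting: "Analyses and the results on primary outcomes will be reported during year 2025".

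The appendix of the same SAP records the steering committee's decision "to stop inclusion in BEST during spring 2022", with 31 March as the final date and 1752 patients included and operated. The schedule in the protocol and sections 3.1 and 5.5 of the perioperative SAP give the same end date. The appendix revisits power but sets no new date for the primary analysis.

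On the length of follow-up, SAP v5 section 3.1 says: "The follow-up time for the primary objectives is 5-years". Section 3.4 places the evaluation of the primary objectives after five years. Section 5.4 censors event-free patients at their individual five-year date, or earlier at withdrawal of consent, emigration or death. Section 5.2 rules out formal interim analyses of the primary outcomes. The protocol (Secondary outcome measures) accepts five-year visits within 6 months either side of the target date.

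Section 5.5 of the perioperative SAP adds that "the results on primary outcomes will be reported during spring 2023".

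**The concern.** Section 5.5 is the only timing section for the primary analysis, and its dates cannot all be true given the actual end of inclusion. It ties completion for every participant to a date at which many of them will not have reached five years.

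Both primary outcomes depend on five years of observation. If the dates were followed, three things would go wrong.

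- **Adverse events.** Patients short of five years would have to be censored at the data cut. Section 5.4 has no such administrative censoring rule, so the analysis would depart from the SAP. The hazard ratio would also give less weight to years four and five.
- **Weight.** Patients not yet due for a five-year visit would still enter the mixed model, and their contribution at five years would rest on the model. In the last-observation-carried-forward sensitivity analysis, their earlier weights, two-year weights at best, would stand in for five-year weights.
- **Repeated looks.** An analysis on the stated dates and another at full follow-up would amount to an interim analysis, which section 5.2 excludes and for which no alpha is set aside.

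**Working it through.** **Inputs from the documents**

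- Planned end of recruitment: June 2019 (SAP v5, 5.5).
- Start and end of inclusion: 6 October 2015 and 31 March 2022 (perioperative SAP, 3.1), which is 2368 days.
- Included and operated: 1752 (SAP v5, appendix).
- Patients with two-year data in February 2022: 1031 (SAP v5, appendix).
- Five-year visit window: 6 months either side (protocol, Secondary outcome measures).

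**Step 1: reproduce the plan's date.** June 2019 + 5 years = June 2024. This is the summer 2024 of section 5.5, so the date comes from the superseded recruitment plan.

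**Step 2: repeat with the actual end of inclusion.** 31 March 2022 + 5 years = 31 March 2027. Adding 6 months gives 30 September 2027.

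**Step 3: follow-up of the last patient on the stated timetable.** From 31 March 2022 to 31 December 2024 is 2.75 years.

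**Step 4: share of the cohort without five full years on 31 December 2024.** These are the patients operated after 31 December 2019. The documents give no accrual curve, so this needs assumptions.

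*(a) Uniform accrual (assumption).* From 6 October 2015 to 31 December 2019 is 1547 days.

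- 1547/2368 = 0.653, and 0.653 × 1752 ≈ 1145 operated by then.
- 1752 − 1145 = 607 without five years (35%).
- For weight, a visit at 4.5 years is acceptable, so the limit moves to 30 June 2020 (1729 days). 1729/2368 = 0.730, which leaves 473 (27%).

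*(b) Anchored on the 1031.* Patients with two-year data in February 2022 were operated by about the end of February 2020 (1607 days from the start). If a fraction r of those due had two-year data (assumption), 1031/r had been operated by then. Taking accrual as uniform up to February 2020, 1547/1607 = 0.963 of these were operated by the end of 2019.

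| Assumed r | Operated by end Feb 2020 | Operated later | Without 5 years at 31 Dec 2024 |
|---|---|---|---|
| 100% | 1031 | 721 (41%) | 759 (43%) |
| 90% | 1146 | 606 (35%) | 649 (37%) |
| 80% | 1289 | 463 (26%) | 511 (29%) |
| 70% | 1473 | 279 (16%) | 334 (19%) |

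The lowest figure, 16%, counts only patients operated after February 2020 at r = 70%. The highest, 43%, takes r = 100% and the end-of-2019 limit.

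**Step 5: plausibility of the upper end.** The period to the end of February 2020 is about 52.8 months, and the remainder to 31 March 2022 about 25 months. At r = 100%, accrual would be 1031/52.8 ≈ 20 a month before and 721/25 ≈ 29 a month after. The appendix says the pandemic severely hit recruitment in 2020–2021, so a rise is unlikely. At r = 80% the rates are 1289/52.8 ≈ 24 and 463/25 ≈ 19, which fits that account better.

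**The case against.** The strongest reply is that this is a stale calendar and nothing more. Section 5.5 is sequential: follow-up is completed for everyone, then data are prepared, then results are reported. Sections 3.4, 5.2 and 5.4 all imply complete five-year follow-up and no early look. The body of the SAP is visibly an older plan updated by an appendix, since section 3.1 still gives 2100 patients. On this view a date has slipped and the analysis rule has not changed. Most of this stands, and it is the likeliest explanation. What remains is that section 5.1 points the reader to the appendix while 5.5 does not, that the appendix gives no replacement date, and that nothing says which prevails when the date and complete follow-up conflict.

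Three stronger readings are tempting, and the documents do not support them.

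- *That an early primary analysis is planned.* A reader might infer this because the appendix computes power from the 1031 patients with two-year data (1031 × 0.80 / 2 ≈ 412; the appendix states 413 per group), who reach five years by about early 2025. No text limits the primary analysis to those patients, and section 5.4 bases the primary conclusions on all randomised patients apart from those who withdraw consent.
- *That late events would be lost for everyone operated after 2019.* Register linkage (sections 3.4 and 5.4) would still capture events up to any cut. A patient operated in January 2020 would have about 4.9 years of event data by the end of December 2024. Only events after the cut would be missing.
- *That five-year results are announced for spring 2023.* The perioperative SAP covers baseline, surgery and 30-day data and calls its analyses exploratory. Its mention of primary outcomes is a wording slip.

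**Conclusion.** The contradiction is certain and lies in current text: section 5.5 against the appendix of the same SAP, the protocol schedule and the perioperative SAP. Completion of five-year follow-up falls in 2027, about 2.6 to 2.75 years after summer 2024 for the last anniversary, and about half a year later again with the visit window.

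The harm is conditional on the stated dates being followed, which the rest of the SAP makes unlikely. In that case roughly 16% to 43% of the 1752 patients would lack five full years at the end of December 2024. The range rests on assumed two-year completeness of 70% to 100% or on uniform accrual, not on a documented figure, and its upper end fits poorly with the pandemic slowdown. For weight the share is somewhat lower, because visits from 4.5 years count.

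No model, margin, significance level or censoring rule is wrong on this account. The section still needs correcting, because it is the SAP's only statement on when the primary analysis takes place and it cannot be met as written.

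**What to change.** In SAP v5 section 5.5:

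1. Replace the dates with ones derived from 31 March 2022: last five-year anniversary 31 March 2027, visit window closing about 30 September 2027, with data preparation and reporting after that.
2. State the rule as well as the dates: the primary data are locked only once the five-year visit window of the last operated patient has closed and the Swedish and Norwegian register extracts cover that period.
3. State that complete follow-up governs if it conflicts with a calendar date, and refer to the statement in section 5.2 that there are no formal interim analyses of the primary outcomes.

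In section 5.5 of the perioperative SAP, change *primary outcomes* to *perioperative outcomes*.

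The cost is wording only. The primary report moves from 2025 to after September 2027, which the five-year endpoints already require for patients included in March 2022.
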